## Abstract

**Background::**

The prevalence of chronic kidney disease (CKD) has been rapidly increasing and has become one of the most concerned global health problems. It is of good importance to improve therapeutic efficiency of CKD and delay disease progression to end stage renal disease (ESRD). Traditional Chinese Medicine (TCM) is a widely used complementary therapy for patients with CKD. The aim of this study is to evaluate whether basic treatment combined with Chinese herbs mixture Qi Gui Yi Shen decoction could achieve better therapeutic effect on CKD patients.

**Methods::**

To determine whether traditional Chinese medicine Qi Gui Yi Shen decoction could achieve better therapeutic effect, we will conduct a randomized controlled trial. A total of 100 CKD patients that meet the inclusion criteria will be enrolled and divided into 2 groups: Qi Gui Yi Shen group (QGYS group) and placebo group. Each group will receive 6-monthly basic treatment in combination with TCM or placebo 3 times per day. Efficacy of Qi Gui Yi Shen decoction is evaluated by analyzing renal function and TCM symptoms, other efficacy assessments include serum level of PAI-I, expression of transforming growth factor beta1 (TGF-beta1). Routine blood count, plasma albumin (ALB), and alanine transaminase (ALT) are evaluated as side effect and safety profile.

**Discussion::**

The results from the clinical trial will provide evidence for the effectiveness and safety of Qi Gui Yi Shen Decoction as a treatment for CKD patients. Furthermore, this will propose a new theory and method for CKD treatment.

**Trial registration::**

Registered with Chinese Clinical Trials Registry at www.chictr.org. (Registration number: ChiCTR1900021622) on 1 March 2019.

## Introduction

1

Chronic kidney disease (CKD), also called chronic kidney failure, is described as a sustained reduction in glomerular filtration rate or evidence of structural or functional kidney abnormalities.^[1]^ According to the current international guidelines, CKD is defined as glomerular filtration rate (GFR) <60 ml/min per 1.73 m^2^ or markers of kidney injuries or both, of at least 3 months duration.^[2]^ CKD is associated with a significantly increased risk of hospital admission, morbidity, and mortality due to cardiovascular disease,^[3]^ and other complications including kidney-disease progression, acute kidney injury, cognitive decline, anemia, mineral and bone disorders, and fractures.^[4]^ Treat or not, a certain number of CKD patients would still progress to the most severe form: end stage renal disease (ESRD). The only therapeutic option for ESRD is renal replacement treatment (RRT): dialysis or transplantation. However, the mortality of patients on dialysis can be as high as 20% per year and transplantation is limited by organ shortage.^[5]^ With people's lifestyle changing, the common risks of CKD nowadays are mainly diabetes, hypertension, old age, and cardiovascular disease.^[6]^ However, no matter what causes CKD, renal fibrosis is the final common consequence and can be hardly reversed.^[7]^ Renal fibrosis now is believed to be a wound healing response to tissue damage and is usually characterized by glomerulosclerosis and tubulointerstitial fibrosis.^[8]^ Glomerulosclerosis manifests as vascular damages and loss of capillaries which will accelerate renal epithelial cells injury for nutrient intake limitation from vessels and finally leads to cell death, epithelial-to-mesenchymal cell transition and inflammatory cytokines release from these cells.^[9,10]^ Besides, overwhelming inflammatory response, in turn, leads to glomerulus impairment. Interstitial inflammation and renal tubular injury also give rise to excessive extracellular matrix (ECM) accumulation and collagen production, thus finally leads to fibrosis generation.^[11,12]^

In recent years, the prevalence of CKD has been rapidly increasing and has become one of the most concerned global health problems. In high-income countries the prevalence of CKD is about 11%. According to the epidemiologic investigation by Peking University Institute of Nephrology, the prevalence rate of CKD by 2012 in China was 10.8%.^[13]^ Yet by 2016, the total population of CKD published by National Bureau of Statistic in China reached nearly 147 million.^[14]^ However, the therapeutic options for CKD are very limited, such as protein, salt and lipid intake restriction, blood pressure control and angiotensin II receptor blockers or angiotensin converting enzyme inhibitors administration, and the efficacy is not satisfactory though. Therefore, it is of great importance to find effective and safe approaches to prevent or interfere disease progression from an early stage. Literature have suggested that for a long time Traditional Chinese Medicine (TCM) could postpone CKD progress while alleviate drug toxicity and side effects, thus improving patients’ survival and life quality.^[15]^

With the emerging worldwide interest in Chinese herbs, researchers conduct in vitro and vivo studies which have confirmed the biological activity and therapeutic effects of several Chinese herbs.^[16]^ Astragalus membranaceus (Huangqi in Chinese), for instance, is reported to be able to reduce proteinuria both in clinical and lab studies,^[17]^ and could also reduce serum cholesterol, improve immune function by regulating T cells and extenuate renal fibrosis.^[18]^ Angelica sinensis (Danggui in Chinese) is another widely studied Chinese herb, it has been shown with the ability of attenuating kidney impairment by suppressing oxidative stress and inflammation.^[19]^ Chinese herbs used for kidney diseases treatment is usually prescribed following different principles such as clearing heat and eliminating dampness and coordinating Yin and Yang in the body and the prescription varies by people of different sexes, ages, natural stamina to their different TCM clinical symptoms.^[20,21]^

Based on our years of clinical and experimental works in TCM, we suggest that through reinforcing spleen and kidney function and activating blood circulation, TCM could postpone CKD progress. According to that theory, we invented QGYS and it has been proven to be able to protect renal function and alleviate renal fibrosis in mouse experiments.^[22,23]^ We also conducted clinical researches on IgA-nephropathy patients and QGYS decoction achieved ideal therapeutic effects.^[24]^ This formula aims to treat Qi deficiency in spleen and kidney, which presents symptoms as sore waist and knee, hard breathing, spontaneous perspiration, pale face and hypodynamia, and so on. This decoction is of independent intellectual property rights and we are still searching its potential mechanisms of renal protection.

## Methods/design

2

### Study design

2.1

A randomized, parallel, placebo controlled clinical trial will be conducted (Fig. 1). The protocol adheres to the Recommendations for Interventional Trials (SPIRIT) guidelines. This study aims to evaluate the efficacy and safety of Qi Gui Yi Shen decoction in treatment of patients with CKD. The study will follow the guidelines as illustrated in Figure 1. A total of 100 participants recruited form the First Affiliated Hospital of Soochow University in Suzhou are divided into TCM treatment group and placebo group in 1:1 ratio. Both groups are administrated with conventional western medicine treatment while TCM group receive extra Qi Gui Yi Shen decoction and placebo group receive placebo decoction. Patients take medicine 3 times a day for 2 months as 1 cycle. At the same time drug efficacy and safety will be evaluated. The total duration is 6 months in 3 cycles.

**Figure 1 F1:**
[figure not shown]
Flow diagram of this research.

### Objectives

2.2

The aim of this study is to evaluate the efficacy of conventional western medicine treatment combined with or without Qi Gui Yi Shen decoction in patients with CKD.

### Study criteria

2.3

Patients diagnosed of CKD of stage II-III; TCM diagnose is spleen and kidney deficiency with syndromes as follows.

#### Diagnostic criteria

2.3.1

Diagnostic criteria for CKD and stages: according to NKF-K/DOQI Clinical Practice Guideline by America National Kidney Foundation. Creatinine clearance is calculated according to CG GFR formulas: Ccr = (140−age) × weight × 1.23/Scr (if male) and Ccr = (140−age) × weight × 1.03/Scr (if female) for CKD stage determination.^[3]^

#### TCM syndrome differentiation criteria

2.3.2

TCM syndrome differentiation is based on the Guidance Principles of Clinical Research on new Chinese medicine.^[4]^ Spleen and kidney deficiency syndromes include primary symptoms as weakness in waist and knees, shortness of breath and spontaneous perspiration, pale complexion, feeling spiritless; secondary symptoms including sallow complexion, heaviness of the head, foot edema, cold limbs, incontinence of urine, nocturia, and diarrhea (Table 1).

**Table 1 T1:**
[figure not shown]
Spleen and kidney deficiency syndromes and the corresponding scoring.

#### Inclusion criteria

2.3.3

Patients with kidney function or structure injury for more than 3 months;Patients of stage II-III CKD: GFR:30∼89 ml/min/1.73 m^2^;Patients who have at least 2 main and 1 secondary symptoms of Spleen and kidney deficiency syndrome;Patients who are 18 to 75 years of age;Patients who agree to voluntarily participate in this study and sign informed consent.

#### Exclusion criteria

2.3.4

Patients who have been diagnosed with malignant cancer, sever heart, liver, brain or other organs dysfunction, shock, dehydration;Patients who are receiving emergent dialysis or kidney replacement treatment;Patients who are pregnant or planning to be pregnant;Patients with progressive neurological deficit or severe neurological symptoms;Patients who are judged to be inappropriate for the clinical study by the researchers.

### Interventions

2.4

In addition to conventional western medicine treatment, TCM group will have additional Qi Gui Yi Shen decoction and control group have placebo.

#### Basic treatment

2.4.1

According to Clinical Practice Guideline of CKD and dialysis from NKF-K/DOQI, all the patients are administrated with basic therapies as limiting intake of salt, protein and fat; managing electrolyte disturbance, anemia and coagulopathy as well as controlling blood pressure.

#### Chinese herbal mixture

2.4.2

Apart from basic therapy, patients in TCM group are provided with QGYS decoction deprived from the following herbs: 30 g Radix Astragali, 15 g Radix Angelicae Sinensis, 15 g Radix Achyranthis Bidentatae, 15 g Rhizoma Chuanxiong, 15 g Radix Pseudostellariae, 15 g Rhizoma Atractylods Macrocephalae, 30 g Semen Eutyales, 30 g Fructus Rosae Laevigatae, 30 g Hedyotic Diffusa, 12 g Periostracum Cicadae and 6 g Radix Glycytthizae. Herbs are boiled in 600 to 700 ml water for 30 minutes and condensed into 300 ml decoction. Patients are administrated with 150 ml decoction three times a day after meal for 2 months.

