#### Placebo group

2.4.3

The placebo is made up by 10% of the Chinese herbs mixture, food color, and artificial flavors. Except for the dispensing technician, researchers and patients do not know the content of the drug packages.

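### The 300 ml yield makes two 150 ml servings but three are prescribed daily: read literally, patients take 1.5 preparations (319.5 g of herb) a day, 50% above the listed weights

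*Protocol article*

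**What the plan says.** Section 2.4.2 (Chinese herbal mixture) gives the recipe in three runs: "30 g Radix Astragali, 15 g Radix Angelicae Sinensis, 15 g Radix Achyranthis Bidentatae", then "15 g Rhizoma Chuanxiong, 15 g Radix Pseudostellariae, 15 g Rhizoma Atractylods Macrocephalae", then "30 g Semen Eutyales, 30 g Fructus Rosae Laevigatae, 30 g Hedyotic Diffusa, 12 g Periostracum Cicadae and 6 g Radix Glycytthizae". The yield follows: "Herbs are boiled in 600 to 700 ml water for 30 minutes and condensed into 300 ml decoction". The next sentence gives serving, frequency and cycle length: "Patients are administrated with 150 ml decoction three times a day after meal for 2 months".

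The frequency is the same elsewhere. Section 2.1 (Study design) says "Patients take medicine 3 times a day for 2 months as 1 cycle", and the abstract says "Each group will receive 6-monthly basic treatment in combination with TCM or placebo 3 times per day".

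Section 2.4.3 (Placebo group) defines the comparator through the same mixture: "The placebo is made up by 10% of the Chinese herbs mixture, food color, and artificial flavors". It gives no volumes of its own.

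The article does not say how many preparations serve one patient for one day, or whether the listed weights are a daily amount.

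**The concern.** The yield and the intake stand in adjacent sentences and do not match. A 300 ml preparation is used up after two servings, and the schedule calls for three. A recipe in grams, boiled in well under a litre of water, is easily taken for one patient's daily supply. On that reading there is no third serving to give.

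The daily dose of the experimental treatment is at stake. Under section 2.4 the decoction is the only treatment meant to differ between the arms. If the listed weights are the intended daily amount, dispensing to the printed volumes gives half as much again of every herb. If the printed volumes are intended, someone who treats the recipe as a daily amount gives a third less than planned.

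**Working it through.** The article states no daily herb total, so there is no figure of its own to reproduce. The inputs are the eleven weights, the yield, the serving volume and the frequency, all from section 2.4.2. The frequency is confirmed in section 2.1 and the abstract.

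**1. Weight of one preparation**
- 30 + 15 + 15 + 15 + 15 + 15 + 30 + 30 + 30 + 12 + 6 = 213 g (11 herbs)

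**2. Servings per preparation**
- 300 ml / 150 ml = 2

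**3. Daily volume and preparations needed**
- 3 × 150 ml = 450 ml a day
- 450 / 300 = 1.5 preparations a day

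**4. Daily herb dose, printed volumes taken literally**
- Concentration: 213 / 300 = 0.71 g/ml
- Per serving: 0.71 × 150 = 106.5 g
- Per day: 3 × 106.5 = 319.5 g (check: 1.5 × 213 = 319.5 g)

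**5. Daily herb dose if one preparation is one day's supply (a premise the article does not state)**
- Per day: 213 g
- Per serving, three times a day: 213 / 3 = 71 g, in 300 / 3 = 100 ml

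**6. Comparison**

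| | Printed volumes | One preparation a day |
|---|---|---|
| Volume per day | 450 ml | 300 ml |
| Herb per serving | 106.5 g | 71 g |
| Herb per day | 319.5 g | 213 g |
| Radix Astragali per day | 45 g | 30 g |

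The ratio is 319.5 / 213 = 1.5. In the other direction, 213 / 319.5 = 0.67, a third less.

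The frequency is an unlikely source of the mismatch, since all three places agree on it. What remains is the yield, the serving volume, or a batch rule that the article leaves out.

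**The case against.** The strongest reply is that nothing here is contradictory. The article gives a recipe with its yield and then a dosing rule, and never says that 300 ml is a day's supply. Decoction can be made in batches and portioned, and the dispensing technician and drug packages in section 2.4.3 are compatible with that. Then 1.5 preparations per patient per day is only a ratio, and batch size and dispensing instructions are details that an article leaves to the full protocol.

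Much of this stands. A reader might infer that the numbers are impossible or that they fix no dose. Neither follows: weights, yield, serving and frequency together give 319.5 g a day, while 213 g needs an added premise. A reader might also infer that patients will receive 50% too much. That holds only if 213 g is the intended dose, which the article does not say.

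Nor should the point be carried into grams of herb in the placebo. That would assume that the 10% is by herb weight and that the placebo is taken in the same volumes, and the article states neither.

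The reply does not remove the mismatch. The article chose to print all four quantities, and they work together only at one and a half times the recipe per day, which it never mentions. That is a discrepancy between stated numbers as well as an omitted detail.

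**Conclusion.** The point holds as a mismatch between the stated yield and the stated intake, and it should be fixed. Read literally, section 2.4.2 prescribes 319.5 g of crude herb a day, 50% above the 213 g it lists. If 213 g is meant as the daily amount, the yield or the serving volume is misprinted. The arithmetic is certain. Which dose is intended cannot be settled from the article.

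The consequence is limited. This is one centre, the randomised comparison and the sample size do not depend on the volumes, and no safety problem is shown at either dose. What suffers is the description of the treatment, because a reader cannot be sure which daily dose a result belongs to.

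**What to change.** State the intended daily crude-herb dose in section 2.4.2 and make the volumes agree with it, keeping three doses a day as in section 2.1 and the abstract.

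- **If one preparation a day is intended (213 g):** change the serving to 100 ml three times a day from the 300 ml yield, or change the yield to 450 ml taken as 150 ml three times a day.
- **If the printed volumes are intended (319.5 g):** keep them and add that a day's dose is 1.5 preparations, 319.5 g.

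Say in section 2.4.3 that the placebo is taken in the same volumes, and check the dispensing instructions against the chosen version. The cost is one corrected volume or one added sentence, plus that check. Sample size and analysis do not change.

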#### Placebo group

2.4.3

The placebo is made up by 10% of the Chinese herbs mixture, food color, and artificial flavors. Except for the dispensing technician, researchers and patients do not know the content of the drug packages.

### Sample size

2.5

Sample size is determined for *t* test. To obtain a power of 90% (α = 0.05), and considering a drop-out rate of 20%, the total sample size required is determined to be 98, 49 in each group.

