### Outcome measures

2.8

The primary outcome measure for this study is renal function and including estimated glomerular filtrate rate (eGFR), serum creatinine (Scr), blood urea nitrogen (BUN) and urinary protein creatinine ratio. They will be measured every 2 to 4 week.

The secondary outcomes include TCM symptoms changes (Table 2), cardiovascular function, lipid profile including triglyceride (TG), total cholesterol (TC), low density lipoprotein (LDL), high density lipoprotein (HDL), as well as serum levels of inflammatory mediators [i.e., TNF-α, IL-1β, IL-8, monocyte chemotactic protein-1 (MCP-1)].

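### The 90% power is for one t test at 0.05, but four unranked variables are primary with no combining rule, so the stated power and 5% error cannot both hold for the primary outcome

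*Protocol article*

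**What the plan says.** In the Protocol article, section 2.5 (Sample size) opens with "Sample size is determined for *t* test". It continues with "To obtain a power of 90% (α = 0.05", closing the bracket there, and ends with "considering a drop-out rate of 20%, the total sample size required is determined to be 98, 49 in each group". It does not say which variable or time point the test concerns. Section 2.1 (Study design) enrols 100 patients who "are divided into TCM treatment group and placebo group in 1:1 ratio", which covers the 98.

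Section 2.8 (Outcome measures) says: "The primary outcome measure for this study is renal function and including estimated glomerular filtrate rate (eGFR), serum creatinine (Scr". The list goes on to blood urea nitrogen and the urinary protein-to-creatinine ratio. All four are measured repeatedly, at intervals of two to four weeks. None is put first, no visit is named as primary, and nothing says whether success means one of the four, all four, or a particular one.

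Section 2.9 (Statistical analysis) compares groups by analysis of variance, or by a Wilcoxon test for non-parametric data. It sets a single significance threshold of P < .05 and mentions no baseline covariate.

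**The concern.** Power and type I error belong to a defined test or decision rule. Section 2.5 supplies one test, section 2.8 supplies four candidates for it, and section 2.9 gives a threshold but no rule. A reader cannot tell what the 90% and the 5% refer to.

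Two misreadings follow. One significant variable out of four could be reported as success at the 5% level when the real chance of a false success is two to almost four times that. Conversely, failure to show all four could be read as a negative result from a 90%-powered trial when the power for that goal was lower.

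**Working it through.** **Inputs.** From section 2.5: power 90%, α = 0.05, drop-out 20%, 49 per arm, t test. From section 2.8: four primary variables. From section 2.9: P < .05. Assumptions: the test is two-sided (sidedness is not stated), and the four test statistics are equally correlated, with correlation ρ between 0 and 0.8.

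**1. Reproducing the stated number.** No difference or SD is given, so the effect is back-solved.

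- Evaluable per arm: 49 × 0.8 = 39.2, taken as 39.
- Normal approximation: d = (1.960 + 1.282) × √(2/39) = 0.734. The exact noncentral t gives d = 0.744.
- Forward check with d = 0.74: n = 2 × (1.960 + 1.282)² / 0.74² = 38.4, rounded up to 39. Then 39 / 0.8 = 48.75, rounded up to 49 per arm, and 2 × 49 = 98.

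So 98 is right for one t test at about 0.74 SD. If α were one-sided, the difference would be about 0.67 SD. If drop-out had been added as n × 1.2, the difference would be 0.72 to 0.73 SD.

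**2. Any one of four at 0.05 each.** Power is at least 90%, but the error rate is not 5%. With independent variables the family-wise error is 1 − 0.95⁴ = 18.5%. Simulation of correlated test statistics gives about 16% at ρ = 0.5 and 11% to 12% at ρ = 0.8.

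**3. All four at 0.05 each.** The error is controlled, but power falls. With every variable at the planned effect and independent, power is 0.9⁴ = 66%. Simulation gives 74% at ρ = 0.5 and 81% at ρ = 0.8.

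| Correlation | Any of four: family-wise error | All four: power |
|---|---|---|
| 0 | 18.5% | 66% |
| 0.5 | 16% | 74% |
| 0.8 | 11–12% | 81% |

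Even at ρ = 0.9 the simulated figures are 9.4% and 84%. These figures count one test per variable; choosing among visits would add further tests.

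**4. Splitting α.** With 0.05 / 4 = 0.0125 per variable, the power for one given variable at d = 0.744 is 76%. Restoring 90% needs 54 evaluable per arm: 54 / 0.8 = 67.5, so 68 per arm and 136 in total. If success is any one of four at 0.0125 and all four variables carry the effect, power is 99.7% at ρ = 0, 96% at ρ = 0.5 and 90% at ρ = 0.8.

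**5. Illustration for eGFR.** The only information on spread is the entry criterion "Patients of stage II-III CKD: GFR:30∼89 ml/min/1.73 m^2", which is not an outcome SD. For assumed final-value SDs of 10, 15 and 20, 0.744 SD is 7.4, 11.2 and 14.9 ml/min/1.73 m² without adjustment. Baseline adjustment multiplies the detectable difference by √(1 − r²). With an assumed r = 0.8 the factor is 0.6, which turns 0.744 SD into about 0.45 SD.

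**The case against.** The strongest reply is that section 2.5 contains no arithmetic error. It claims 90% for a t test and gives a number that one t test reproduces. It never claims 90% for renal function as a whole. That stands, and 98 should not be called wrong.

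A second reply is that some rules keep both properties. Any-of-four with a Bonferroni split holds about 90% or more for ρ up to 0.8 if all four variables carry the effect. A fixed testing order keeps 90% for the first variable. That also stands, but the article states neither rule, and its only threshold is 0.05. A reader might infer that 90% power has been shown to fail for the four-variable outcome. The document does not support that: power fails under an all-four rule, or for one pre-named variable at 0.0125, and is otherwise undefined until a rule is given.

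A third reply is that an article may leave the difference, the SD and the multiplicity method to a fuller document. Their absence alone is therefore not the point. The point rests on what the article does fix: one test, four unranked primary variables and one threshold.

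A reader might also infer that the trial is underpowered for a realistic eGFR effect. The document gives no expected eGFR difference and no SD, and it does not say whether final values or changes are compared. The eGFR figures above are illustrations under assumed SDs and carry no verdict on plausibility.

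**Conclusion.** The point holds as a mismatch between the sample size statement and the primary outcome. At P < .05 for each variable, any-of-four success costs the 5% error (about 11% to 19%), and all-four success costs the 90% power (66% to 81%). The ranges rest on a two-sided α, 39 evaluable per arm, a true effect of about 0.74 SD on each variable for the power figures, and a common correlation between 0 and 0.8. They do not depend on any assumed eGFR SD. The sample size itself is internally coherent, and no claim is made about which effect size is plausible.

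**What to change.** Keep the 98 to 100 patients and take one of two routes.

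- **Single primary.** Name one of the four variables (for example eGFR) at one time point (for example end of treatment at 6 months) and move the other three to secondary. Analyse it by ANCOVA adjusted for its baseline value. State in section 2.5 that the 90% applies to that test, at a difference of about 0.74 SD before adjustment, and give the difference and SD behind it.
- **Four primaries.** State a rule that controls the error across the four and restate the power under it. For a Bonferroni split that is 76% for a given variable at α = 0.0125 with the present numbers.

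The first route needs no extra patients and no extra measurements. Its real cost is that three declared primary variables become secondary and the analysis in section 2.9 changes, so it is more than a rewording. It should be settled before any unblinded data are seen. The second route keeps all four primary, at the price of a lower stated power for each or, to restore 90% for a given variable, 136 patients.
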